### Secondary Objective

---

Re-intervention rate (including implant removal) after 1-year follow-up.

---

---

All other complications (including complications treated non-operatively)

- Fracture related infection.
- Symptomatic non-union defined as absence of radiological signs of healing (callus formation or fading of fractures lines) combined with pain at the fracture site at 9 months.
- Asymptomatic non-union defined as absence of radiological signs of healing (callus formation or fading of fracture lines) without any clinical symptoms.
- Numbness below scar line related postoperatively and at 12-months follow-up.
- Self-reported implant irritation or other reasons for implant removal at 12 months.

Operative time.

Length of surgical incision.

QuickDASH score at baseline (pre-injury), 3- and 12-months follow-up.

EQ-5D-5L at baseline (pre-injury), 3- and 12-months follow-up.

VAS pain and patient satisfaction at 3- and 12-months follow-up.

---

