## 32 **Background**

33 Exposed to the exterior environment due to a lack of surrounding muscles or subcutaneous tissue, the  
34 clavicle is prone to traumatic injury. Clavicle fractures account for 5 to 6% of all fractures, of which  
35 69 to 81% occur in the midshaft. [1,2] Surgical stabilization using a single plate, positioned either  
36 anteriorly or superiorly, is the most common surgical technique when patients/surgeons decide on  
37 operative treatment. [3] The major disadvantage of plate fixation, however, is implant irritation. As a  
38 result, up to 64% of patients undergo re-interventional surgery for implant removal. [4]

39

40 In recent years a low-profile double plating technique with smaller plates has been described as a  
41 possible solution to reduce the high rates of implant irritation. [5] Biomechanically, low-profile dou-  
42 ble plating is expected to be at least as stable as single plating. [6] A recently published meta-analysis  
43 showed that low-profile double plating for midshaft clavicle fractures is a safe procedure attaining  
44 the same high union rates seen in patients treated with single plating. [7] Additionally, double plating  
45 appears to have a lower overall complication and reintervention rate, mainly due to the lower  
46 incidence of implant-related complaints. Low-profile dual plating, however, is a relatively new  
47 technique and should be further explored to test whether our findings can be confirmed.

48

Although randomized controlled trials (RCTs) are considered the gold standard for testing the effectiveness of such new interventions, the artificial conditions that are usually imposed on surgical practice frequently limit the feasibility and the generalizability of its results. A natural experiment (NE) design offers a possible solution. NEs are observational studies in which patients are exposed to either the experimental or the control condition, and treatment allocation is determined by factors outside the control of the investigators (e.g., geographical location). [8] Although not the same, the process governing treatment allocation arguably resembles that of randomization, since treatment allocation is expected to be (to a large extent) independent of patients' characteristics and their prognosis.

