## **Methods/Design**

### **Aim**

To compare single plating to low-profile double plating in midshaft clavicle fractures with regard to re-intervention, complications, healing, quality of life, functional results, and cost-effectiveness.

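### Read literally, Table 1's two non-union definitions are not exhaustive: an unhealed patient with a symptom other than fracture-site pain, and without that pain, meets neither

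*Protocol*

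**What the plan says.** The Aim names healing as one of the comparisons: "To compare single plating to low-profile double plating in midshaft clavicle fractures with regard to re-intervention, complications, healing". Table 1 lists no measure of healing other than non-union, which it defines in two parts among the secondary outcomes.

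- Symptomatic: the X-ray must be unhealed, and this finding must be "combined with pain at the fracture site at 9 months".
- Asymptomatic: "Asymptomatic non-union defined as absence of radiological signs of healing (callus formation or fading of fracture lines) without any clinical symptoms". No time point is given.

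There is no third category, no overall definition of non-union, and no rule for a patient whose symptom is something other than pain. The same list records two such symptoms as items of their own. One is numbness: "Numbness below scar line related postoperatively and at 12-months follow-up". The other is irritation: "Self-reported implant irritation or other reasons for implant removal at 12 months".

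The Background says of plates in general: "The major disadvantage of plate fixation, however, is implant irritation". Of double plating it says: "appears to have a lower overall complication and reintervention rate, mainly due to the lower"; the sentence goes on to name complaints related to the implant.

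X-rays are planned at six weeks, three months and one year (Standardization of care). Table 2 shows them at baseline, 12 weeks and 12 months. None falls at 9 months.

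**The concern.** One definition asks for a particular symptom and the other for the absence of every symptom. A pair built that way need not cover all unhealed fractures. If the healing result is the sum of the two categories, patients in between drop out of it.

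The patients in between are those with non-pain symptoms, and the protocol expects one such group, implant complaints, to be smaller with double plating. If that also held among unhealed patients, more single-plate than double-plate non-unions would go unlabelled, and double plating would look relatively worse on healing than it is.

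A related gap concerns timing. The symptomatic definition is fixed at 9 months, so a patient re-operated earlier for failed healing, whose fracture has united by then, does not meet it.

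**Working it through.** **Classification.** The protocol states no non-union rate, so there is no figure to reproduce. Take only patients without radiological healing and apply both definitions to every combination of fracture-site pain and any other clinical symptom.

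| Fracture-site pain | Other symptom | Symptomatic | Asymptomatic | Result |
|---|---|---|---|---|
| no | no | no | yes | asymptomatic |
| yes | no | yes | no | symptomatic |
| yes | yes | yes | no | symptomatic |
| no | yes | no | no | neither |

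One combination of four is unlabelled. A patient with both pain and another symptom is counted, so the gap concerns only other symptoms without fracture-site pain.

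**Illustration of size.** The protocol gives none of the rates needed, so r and q below are assumptions.

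- n = 168 per arm: 336 / 2 from the sample size section. An equal split is itself an assumption, since allocation follows location.
- r: true radiological non-union, set equal in both arms.
- q: share of non-unions in the unlabelled combination, single (qS) and double (qD).
- Counted = n × r × (1 − q). Apparent ratio, double to single = (1 − qD) / (1 − qS). The true ratio is 1.00.

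| r | True per arm | qS / qD | Counted single | Counted double | Apparent ratio |
|---|---|---|---|---|---|
| 2% | 3.36 | 10% / 10% | 3.02 | 3.02 | 1.00 |
| 2% | 3.36 | 30% / 10% | 2.35 | 3.02 | 1.29 |
| 2% | 3.36 | 50% / 20% | 1.68 | 2.69 | 1.60 |
| 5% | 8.40 | 10% / 10% | 7.56 | 7.56 | 1.00 |
| 5% | 8.40 | 30% / 10% | 5.88 | 7.56 | 1.29 |
| 5% | 8.40 | 50% / 20% | 4.20 | 6.72 | 1.60 |
| 10% | 16.80 | 10% / 10% | 15.12 | 15.12 | 1.00 |
| 10% | 16.80 | 30% / 10% | 11.76 | 15.12 | 1.29 |
| 10% | 16.80 | 50% / 20% | 8.40 | 13.44 | 1.60 |

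Worked line: 168 × 0.05 × 0.70 = 5.88 and 168 × 0.05 × 0.90 = 7.56; 0.90 / 0.70 = 1.29.

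A second way to set q: suppose half of non-unions lack fracture-site pain and, of those, 40% (single) and 15% (double) have another symptom. Then qS = 0.5 × 0.40 = 20% and qD = 0.5 × 0.15 = 7.5%. With r = 5%, the counted rates are 5% × 0.80 = 4.0% and 5% × 0.925 = 4.6%, or 6.72 against 7.77 patients, a difference of about one.

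With r up to 5% and q up to 30%, at most 8.40 × 0.30 = 2.5 patients are lost in an arm. The largest loss in the table, 16.80 × 0.50 = 8.4, needs 10% non-union with half of it in the unlabelled combination. With equal shares both arms lose the same proportion and the ratio is undisturbed.

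**The case against.** The strongest reply is that the absence of clinical symptoms, in a definition of asymptomatic non-union, naturally means symptoms of the non-union. Numbness and implant irritation have their own lines in the table, so a numb scar need not stop a non-union from being asymptomatic. On that reading only painless loss of function is left out. This is a fair reading and it shrinks the gap, but the wording excludes any symptom and no text narrows it. Two centres favour each technique, so a difference between centres in how the wording is read would largely coincide with treatment.

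A reader might infer that these patients are counted nowhere. The protocol does not support that. The complications list is introduced by way of example, complications are collected at 12 weeks, 12 months and 24 months, and all adverse events are registered. What is lost is the non-union label, not the patient.

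A reader might also infer that the healing comparison is biased against double plating. That is not shown. The Background speaks of implant complaints overall, not of irritation without fracture-site pain among unhealed patients, and it gives no arm difference for numbness. Irritation felt as pain at the fracture would be counted as symptomatic. The asymptomatic definition has no time point, so it could pick up fractures still healing and offset part of the loss.

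Nor are early healing failures hidden from the trial. The primary outcome takes re-interventions for every indication, so an early revision counts there; it is missing only from the 9-month symptomatic category.

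Finally, scheduled X-rays would allow total radiological non-union to be reported whatever the symptom label, and a SAP not shown here might do so. That is why the remedy is cheap. The protocol nonetheless fixes the two definitions itself and states no total.

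**Conclusion.** The point holds in a limited form. Taken as written, the two definitions leave one combination without a label, so non-union counted as their sum can be understated. Whether the loss differs by arm is conditional: plausible for implant complaints, not demonstrated among non-unions.

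The size cannot be derived from the protocol. Under moderate assumptions it is one to three patients in an arm, and probably a few at most. For comparison, with r = 5% the chance standard deviation of the count in one arm is √(168 × 0.05 × 0.95) = 2.8 patients. The outcome is secondary; the primary outcome, sample size and power do not change. The early re-operation gap is real for the symptomatic category only. Severity: minor.

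**What to change.** In Table 1:

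1. Make total radiological non-union, meaning no radiological healing whatever the symptoms, the healing outcome. Assess it at one common time point that has a scheduled X-ray; the only one planned after 9 months is at 12 months.
2. Split that total into two complementary categories, with and without fracture-site pain, both at the same time point. Rewording the asymptomatic definition alone would not be enough, because only the symptomatic one now carries a time point.
3. Count a recorded re-intervention for failed healing before that time point as a non-union event in the total.

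This needs no new visit, X-ray or patient, but the indication for each re-intervention must be recorded. Reported non-union rates may rise slightly, and the group without pain will include some patients with other symptoms, so it should not be called asymptomatic.

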**Table 1: Primary and secondary outcomes.**

**The outcome measure, follow-up and timeline**

At baseline, the treating physician or local investigator will collect the following characteristics: age, gender, body mass index (BMI), smoking status, comorbidities, medication, trauma mechanism, concomitant injuries and planned operative procedure (including treating hospital and surgeon), pre-injury DASH and EQ-5D-5L. The x-ray at presentation or outpatient clinic visit will be used to determine fracture type and dislocation. Fracture type will be determined according to the AO/OTA classification system for midshaft clavicle fractures. [9] Patients will receive the operation within two weeks of presentation.

The patients will return to the outpatient clinic at three and twelve months. The outpatient clinic visit will include several questionnaires (e.g., VAS, EQ5D, DASH), x-rays, and a physical examination (Table 2). All data and adverse events (AE) will be registered. At two years, the patient will be either

seen at the outpatient clinic visit or interviewed by telephone, and the electronic patient database will be accessed to assess patient-reported outcome measures (PROMS), complications and reintervention rate.

All the measurements and examinations described are part of standard care, except the questionnaires. The questionnaires will be filled in at regular outpatient clinic visits or by telephone interview.

|                            | Baseline (at inclusion) | 12-weeks follow-up | 12-months follow-up | 24-months follow-up |
|----------------------------|-------------------------|--------------------|---------------------|---------------------|
| Re-intervention            |                         |                    | X                   | X                   |
| X-ray                      | X                       | X                  | X                   |                     |
| DASH*                      | X                       | X                  | X                   |                     |
| EQ5D-5L*                   | X                       | X                  | X                   |                     |
| VAS pain and satisfaction* | X                       | X                  | X                   |                     |
| Complications              |                         | X                  | X                   | X                   |

\* Not part of standard care.

## Table 2. Outcome measures and planning

### Sample size calculation

The sample size calculation is based on the primary outcome (re-intervention). Based on a recent meta-analysis of our study group, a risk reduction of 10% is expected in favor of low-profile double plating compared to single plating. To demonstrate this difference using a chi-square-test ( $\alpha =$

0.05, power = 0.8) approximately 152 patients per treatment group are needed. To compensate for a potential 5% loss to follow-up, a total of 336 patients are required.

## **Statistical analysis.**

The statistical package IBM SPSS Statistics for Windows, version 28.0, will be used for analysis. Depending on the normality distribution, baseline characteristics will be described as means and standard deviations or median and interquartile range for continuous variables. Categorical variables will be reported in counts and percentages. Differences between treatment groups will be analyzed with an independent samples student's T-test or Mann-Whitney-U test (depending on distribution). Categorical variables will be analyzed using the Chi-square test.

The primary outcome will be analyzed using logistic regression with revision surgery as the dependent and treatment as the independent variable. The relative risk (RR) will be calculated with a 95% confidence interval (95% CI). Multivariable logistics regression analysis will also be performed to account for potential known confounders including age and fracture type.

Missing data (caused by incomplete hospital documentation or loss-to-follow-up) will be addressed using multiple imputation techniques.

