### *Material & Methods*

Patients ( $\geq 18$  years) with primary midshaft clavicle fractures that are eligible for operative treatment will be included. Treatment allocation will be determined by the geographical location of the accident and local hospital providing treatment. In two centres, single plating is the treatment of choice for these patients. In two others, low-profile double plating has become the standard treatment. For the low-profile double plating group, one superiorly positioned VariAx 2.0mm and one anterior VariAx 2.4mm or 2.7mm plate will be used. For the single plating group, the standard locally available implant will be used. A total of 336 patients will be included. The primary outcome of interest is re-intervention. Secondary outcomes include complications, operative time, length of incision, functional scores (DASH, EQ-5D-DL, VAS-Pain/Satisfaction) and cost-effectiveness.

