### **Study design**

This study will be a multicenter prospective cohort study between four Swiss centers with comparable patient case-mix. At which hospital/surgeon trauma patients are presented after an accident depends on the geographical location of the accident. We hypothesize that different Swiss centers treat a similar caseload of trauma patients with clavicle fracture and that the patient case-mix is similar across the different centers.

73 Of the four participating centers, two centers are specialized in single plating, and two are specialised  
74 in low-profile double plating will participate. Treatments will be naturally allocated by the geograph-  
75 ical location of the accident. Although centers are divided into either category based on their standard  
76 treatment of care, surgeons will be allowed to alter their treatment plan based on their own surgical  
77 expertise and according to what they (after consultation of the patient) consider the most appropriate  
78 treatment. This study design is sometimes referred to as a NE and is arguably less prone to confound-  
79 ing bias than conventional observational studies, provided the above-mentioned assumptions hold.

[figure not shown]

**Figure 1** Schedule of enrolment, interventions, and assessments

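### The lead analysis of a non-randomised comparison is unadjusted; adjustment is secondary with an open covariate list, and no stated analysis uses the pre-injury DASH and EQ-5D scores

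*Protocol*

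**What the plan says.** On allocation, the abstract (Material & Methods) states: "Treatment allocation will be determined by the geographical location of the accident and local hospital providing treatment". Two centres use single plating as standard and two use low-profile double plating. Under Study design the comparability of the centres is put forward as a hypothesis: "We hypothesize that different Swiss centers treat a similar caseload of trauma patients with clavicle fracture". The same section says "surgeons will be allowed to alter their treatment plan based on their own surgical" expertise and what they judge suitable for the patient. It claims lower susceptibility to confounding only on condition that its assumptions hold.

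On the primary outcome, the Statistical analysis section says: "The primary outcome will be analyzed using logistic regression with revision surgery as the dependent and treatment as the independent variable". It then adds: "Multivariable logistics regression analysis will also be performed to account for potential known confounders including age and fracture type".

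On continuous variables, the same section says, directly after describing how baseline characteristics will be summarised: "Differences between treatment groups will be analyzed with an independent samples student's T-test or Mann-Whitney-U test (depending on distribution". No other between-group method for a continuous variable appears.

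On the data available, the section on outcome measures, follow-up and timeline lists "age, gender, body mass index (BMI), smoking status, comorbidities, medication, trauma mechanism, concomitant injuries and planned operative procedure", plus pre-injury DASH and EQ-5D-5L. Fracture type and dislocation are read from the X-ray. Table 1 lists both scores before injury and at 3 and 12 months.

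**The concern.** In a randomised trial a crude comparison of groups is protected by the allocation. Here it is protected only if the patients operated on in the two pairs of centres are alike in what drives re-intervention. The protocol leaves three ways for that to fail:

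- Case-mix may differ between centres. With two centres per technique, such differences do not average out as they would over many individually randomised patients.
- The threshold for operating may differ. The eligibility list for surgery is explicitly not exhaustive, and patients are approached only after the decision to operate.
- A surgeon may choose the other technique for a particular patient, which opens the door to confounding by indication within a centre even where case-mix is equal between centres.

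If any of these occurs, the difference passes straight into the estimate that the protocol names first. An open covariate list adds a second weakness: several adjusted estimates can be produced, and nothing in the protocol says which one counts. For DASH and EQ-5D, a plain two-sample test would carry the same confounding and would give up whatever precision the pre-injury score offers.

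**Working it through.** The protocol gives no figure for this point, so there is none to reproduce. The check sets the text against the design and then sizes the problem under assumed values.

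**Text against design.** Allocation is not randomised, comparability is hypothesised, and departures from the centre's technique are allowed. The first-named primary model contains treatment only, and the multivariable model is additional. Two covariates are named and the list is left open. Sex, BMI, smoking, comorbidities, medication, trauma mechanism, concomitant injuries and dislocation are collected but not named for adjustment. Pre-injury DASH and EQ-5D-5L are collected but appear in no stated analysis.

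**Bias in the crude relative risk.** All inputs are assumptions. Take one omitted binary factor with prevalence a in one group and b in the other, multiplying risk by R, and no true treatment effect. Then

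crude RR = [1 + b(R − 1)] / [1 + a(R − 1)].

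| a | b | R | Crude RR |
|---|---|---|---|
| 30% | 40% | 1.5 | 1.20/1.15 = 1.043 |
| 30% | 40% | 2 | 1.40/1.30 = 1.077 |
| 30% | 50% | 1.5 | 1.25/1.15 = 1.087 |
| 30% | 50% | 2 | 1.50/1.30 = 1.154 |

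The bias is therefore about 4% to 15%.

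**Effect on the test.** With the planned 152 per group, and an assumed risk of 15% in the group where the factor has 30% prevalence, the real two-sided type I error of a nominal 5% test is 5.3% in the first row, 5.9% in the second and 8.5% in the fourth.

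**Baseline score.** Adjusting for a pre-injury score that correlates r with the follow-up score multiplies residual variance by 1 − r². The protocol gives no r. For assumed r = 0.2, 0.5 and 0.6 the factor is 0.96, 0.75 and 0.64, a reduction of 4%, 25% and 36%.

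**Room for covariates.** The Sample size calculation gives a 10% reduction but no group rates. Assumed rates over 2 × 152 = 304 evaluable patients give:

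- 16% vs 6%: 304 × (0.16 + 0.06)/2 = 33.4, about 33 events.
- 30% vs 20%: 304 × (0.30 + 0.20)/2 = 76 events.

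Treatment plus age, sex, BMI, smoking, fracture type and displacement needs at least 7 coefficients. That is 33/7 = 4.7 events per coefficient in the first case and 76/7 = 10.9 in the second.

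**The case against.** Three stronger readings are tempting, and the protocol supports none of them.

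- A reader might infer that the other collected confounders will go unused. The wording gives age and fracture type as examples, so the list is open. A full list may stand in a statistical analysis plan that was not available. What can be said is that the others are not named.
- A reader might infer that DASH and EQ-5D will be compared by t-test. The sentence follows the description of baseline characteristics, names neither score and allows Mann-Whitney as well. Applying it to these outcomes is a reasonable inference, because no other method is given, but it is an inference.
- A reader might infer that confounding is ignored. It is not: an adjusted analysis of the primary outcome is planned, and the protocol openly states the condition on which its design argument rests.

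The defence goes further. A crude lead estimate follows from the natural-experiment rationale, and the sizes shown here are illustrations that say nothing about imbalance in this study. The second half of that is right. The first half is weakened by the protocol's own permission for surgeons to depart from the centre's technique, because that part of the allocation is not geographical.

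It is also fair to say that patient-level adjustment has limits. Technique largely follows centre, so adjusting for patient factors cannot separate technique from centre or surgeon. Adding hospital as a covariate would leave mainly the within-centre departures to estimate the effect, and those are the patients most open to confounding by indication.

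**Conclusion.** The point stands in a limited form. As written, the headline result for re-intervention comes from a model with no protection against confounding, in a study whose comparability is assumed. The adjusted model exists but is in the wrong role, and its covariate set is not fixed. For continuous outcomes the protocol offers only unadjusted two-sample tests, and no stated analysis uses the pre-injury scores.

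The possible size is moderate: about 4% to 15% bias in the crude relative risk for one omitted factor, and a type I error of roughly 5% to 9% in the cases computed. Both rest on assumed prevalences and risk ratios, and the type I error also on an assumed 15% risk. The gain from the pre-injury scores could be small (4% of variance at r = 0.2) or substantial (36% at r = 0.6). The case for change rests on the design, not on these figures.

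**What to change.** - Name the adjusted estimate as primary, and fix its covariates before any outcome data are seen. A short set from what is already collected would do, for example age, sex, BMI, smoking, fracture type and displacement. Report the crude estimate beside it.
- State in advance what happens if events are too few for that set: a shorter list, or a propensity score built from the same variables. A propensity model is limited by the number of patients in each treatment group (152 planned) and not by the number of events.
- Analyse DASH and EQ-5D at 3 and 12 months with a model that includes the pre-injury score and the same covariates.
- State as a limitation that adjustment for patient factors does not remove centre or surgeon effects.

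The change needs no new data, but it does replace the lead primary model and adds models for the scores, so it calls for a protocol amendment. The main downside is the uncertain covariate capacity: about 33 events under assumed rates of 16% vs 6%, about 76 under 30% vs 20%. With the lower count, all six example covariates would be too many for a direct outcome model.
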